### Selection criteria

All adolescent girls and young women aged 15–24 years who have lived in the selected parishes for at least three months and do not plan to leave their respective villages in the next one year will be eligible to participate in this study, after providing informed consent. Eligible peer leaders will be adolescent girls and young women aged 15–24 years, who have lived in their communities for at least six months with no intention to migrate within three months with basic English and Luo comprehension, good communication skills, and are viewed as role models with integrity in their communities. All AGYW with a confirmed diagnosis of HIV/AIDS and/or on antiretroviral therapy prior to this study will be excluded.

### Study procedures

The key phases and procedures of this study are summarized in Fig. 3 below.

**Fig. 3 Fig3:**
[figure not shown]
A schematic description of the study showing the three phases of implementation research

### Formative phase

We will conduct a qualitative exploratory study among AGYW, CHWs, community leaders, and parents and/or spouses of AGYW from the five selected parishes before the intervention. A total of 50 AGYW, 50 parents and/or spouses for married AYGW, and 30 CHWs from five parishes will participate in 5 (FGDs), each with a composition of 10 participants per FGD. This is in line with the literature, which suggests that for FGDs, 4–6 groups are typically sufficient to reach saturation in homogeneous populations, with each group consisting of 6–10 participants [49]. Additionally, 15 community leaders from the five parishes will be selected purposively for in-depth interviews (IDIs). The FGDs and IDIs will explore the participants’ knowledge and perceptions of HIV, experiences with HIV testing services, and preferences regarding peer-led and CHW-facilitated HIVST models. All the FGDs and KIIs will be conducted in Luo and will be recorded. We will also conduct one key-informant interview (KII) with the district health office to explore the landscape surrounding the provision of HIV services in the district, as well as to map potential stakeholders and facilitators of success. Each interview will be moderated/conducted by two research assistants with experience in qualitative research and fluency in both languages after comprehensive training.

The findings from our formative research will lay a crucial foundation for designing the intervention and further adaptation. We shall utilize on-the-go adaptation strategies previously described by Elvin Geng and colleagues to tailor the intervention strategy [50]. The adaptations may involve refining communication messages, adjusting delivery methods, or redefining the roles of peer leaders and CHWs.

### Baseline pre-intervention survey

Before the intervention, 415 AGYW, aged 15–24 years, who have lived in their communities for at least three months, will be selected from the five parishes using systematic random sampling at a household level and administered a baseline semi-structured survey. Sociodemographic data, knowledge, perceptions, and practices on HIV and HTS, including HIVST, will be collected. The questionnaire will also evaluate the feasibility, acceptability, and appropriateness of HIVST and the peer-delivered CHW-facilitated HIVST model.

### Implementation strategy

With the guidance of the community leaders and ten purposively selected CHWs, we will identify 30 AGYWs from the five parishes to serve as peer leaders. The peer leaders and CHWs will undergo comprehensive training on the project, their roles, and the technical aspects of HIV/AIDS, HIVST procedures, basic counselling, and linkage to care. We will also train them in community mobilisation, communication, and engagement. The CHWs will allocate oral HIVST kits (OraQuick™) to peer leaders, who will distribute them to AGYW selected by systematic random sampling in their respective villages over three months. Each AGYW peer leader will then be instructed to distribute HIVST kits to 13 of the selected AGYW from their villages within three months. Adolescent girls and young women who desire to receive additional HIV self-testing kits for their partners/spouses will also be provided.

The kit will also contain informational material in English and Acholi, containing the testing instructions, a confidential results card, and mobile contacts of CHWs, counsellors, and health facility focal persons to support confirmatory testing and ART initiation for those who test positive. Distributions will take place through various strategies, including door-to-door, community group meetings, and at other preferred locations. They will be carried out at different times, including weekends and evenings, to maximise accessibility for AGYW with varied schedules. The peer leaders will demonstrate the HIVST kit usage to the AGYW and remind them to perform the test for up to two weeks following the initial distribution.

The CHWs will then follow up with all the AGYWs who conduct the HIV self-test, seeking their consent for voluntary disclosure of test results and facilitating linkage to confirmatory testing and ART initiation. CHWs will also support community entry, manage logistics, oversee HIVST distribution by peer leaders, and provide continuous support.

### Post-intervention survey

To explore post-intervention acceptability, appropriateness, feasibility, experiences, perceived barriers, facilitators, and overall perceptions toward the peer-delivered and CHW-facilitated HIVST model, we will conduct a follow-up semi-structured survey with all the study participants using a semi-structured questionnaire. Additionally, we shall conduct nine FGDs: five among AGYW who were scheduled to receive the intervention, three among AGYW peer leaders, and one among CHWs. Each FGD will consist of ten participants. We will also track and record the number and trends of HIVST kits distributed through the peer leaders and the CHWs to assess feasibility. Fidelity will be assessed using observational checklists and qualitative feedback from the AGYW, peer-leaders, and the CHWs. We will also track and record all costs associated with the implementation in record-keeping books for an economic evaluation of the model.

### Post-intervention follow-up

We will follow up with all the AGYW who received HIVST kits for up to one month to assess for self-reported use of the HIVST kits. AGYW will also be asked to share their test results with the study team anonymously using confidential cards included in the HIVST kit package to evaluate the positivity rate. We will also track the number of confirmatory tests, linkages to care, and ART initiation among AGYW who test positive using data from the CHWs and the health facility contact persons.

### Study outcomes

The primary outcomes (acceptability and feasibility) and the secondary outcomes (appropriateness, fidelity, and cost) are derived from the Proctor Framework, with details of measurements in Table 1 [51]. Acceptability is defined as the perception by the stakeholders (AGYW, peer leaders, and CHWs) that the model is agreeable or satisfactory. Feasibility is defined as the degree to which the HIVST is successfully distributed through the peer-delivered CHW-facilitated model. Preliminary effectiveness will be defined as the proportions of AGYW who perform an HIV test within one month of HIVST kit reception, are linked for confirmatory testing, and ART initiation.

**Table 1 Tab1:** Implementation outcomes to be evaluated in this study (adopted from the Proctor Implementation Framework)

Outcome	Measurements
Acceptability	• The proportion of AGYW who report the peer-delivered CHW-facilitated HIVST model as agreeable and satisfactory before and after the implementation. • The proportion of peer leaders and CHWs who find the delivery process acceptable. • Qualitative feedback from AGYW, peer leaders, and CHWs.
Feasibility	• The proportion of planned HIVST kit distribution that will successfully be carried out. • Qualitative feedback from CHWs and peer leaders regarding challenges or barriers.
Appropriateness	• The proportion of stakeholders (AGYW, CHWs, community members) who perceive HIVST as a relevant and fitting solution for HIV testing challenges.
Fidelity	• The proportion of CHWs and AGYW peer-leaders who correctly perform all the planned activities during the HIVST distribution. • The proportion of AGYW who will receive all components as planned.
Cost	• Financial and economic costs associated with HIVST kits procurement, training, and distribution (including reimbursing peer leaders and CHWs). • Cost comparison to potential long-term savings or benefits.

### Data management and analysis

The FGDs and KIIs recordings will be transcribed verbatim, translated to English, and exported to *Atlas.ti* for thematic content analysis to inform the development and adaptation of intervention. Transcriptions from the FGDs and KIIs will be thematically analysed to identify themes related to implementation outcomes, experiences, barriers, and facilitators of peer-delivered CHW-facilitated HIVST. Upon importing the transcribed data into Atlas.ti, we will initially conduct a thorough reading to familiarize ourselves with the content, marking significant and recurrent themes related to barriers and facilitators to HIV and HIVST among AGYW in Northern Uganda. Coding will be performed iteratively, with initial codes generated from the data being grouped into broader themes and sub-themes that capture the nuances of participants’ experiences and perceptions.

Quantitative data from the semi-structured questionnaires and observational checklists will be collected by trained research assistants using RedCap™ deployed into a tablet, uploaded on secure cloud storage, and exported to STATA 18.0 and R Software for cleaning, coding, and analysis. At the univariate level, we will describe demographic characteristics and implementation outcomes using frequencies and percentages for categorical variables, means and standard deviation for normally distributed continuous variables, and median and interquartile range for non-parametric distribution. Factors associated with acceptability will be assessed using multilevel logistic regression models, adjusting for confounders. Factors to be included in the model will be selected from the literature review guided by the COM-B, HBM, and CFIR theoretical frameworks and expert opinion. We will also evaluate changes in the implementation outcomes before and after the intervention using paired t-test, Mann-Whiney U test, and McNemar’s Test, appropriately. A *p*-value < 0.05 will be considered statistically significant. We will estimate the overall cost of implementing the intervention using the data recorded in the financial books. The costs per HIV test kit distributed, HIV test performed, and HIV diagnosis will be calculated to facilitate a cost-benefit analysis of the model.

The preliminary effectiveness outcomes that will be assessed include HIV testing uptake, confirmatory HIV testing, and linkage to care. Because of the modest sample size powered to assess acceptability, we will provide descriptive findings on the proportion of AGYW that performed HIV testing after receiving HIVST kits, the proportion that tested positive on confirmatory HIV testing, and the number of AGYW that were linked to care. These results will guide future large-scale controlled trials on the effectiveness of the peer-led CHW-facilitated HIVST model.

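### Before-after tests of AGYW-reported acceptability and appropriateness assume independent pairs although about 13 AGYW share each peer leader, so the nominal 5% test is too liberal if change is correlated within leader

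*Protocol article*

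**What the plan says.** All references are to the protocol article.

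- **Data management and analysis** states: "We will also evaluate changes in the implementation outcomes before and after the intervention using paired t-test, Mann-Whiney U test, and McNemar’s Test, appropriately", with the rule that a p-"value < 0.05 will be considered statistically significant". No adjustment for leader, village or parish is attached to these tests. A multilevel approach appears in the same paragraph, but for another purpose: "Factors associated with acceptability will be assessed using multilevel logistic regression models, adjusting for confounders".
- **Implementation strategy** has the sponsor's team choose the deliverers: "we will identify 30 AGYWs from the five parishes to serve as peer leaders". On workload: "Each AGYW peer leader will then be instructed to distribute HIVST kits to 13 of the selected AGYW from their villages within three months". The same leader demonstrates the kit and reminds recipients to test.
- **Baseline pre-intervention survey** and **Post-intervention survey** both cover acceptability and appropriateness, and the second goes back to the same people: "we will conduct a follow-up semi-structured survey with all the study participants using a semi-structured questionnaire".
- **Study outcomes** (Table 1) makes acceptability primary. For AGYW it is a proportion rated before and after, and what is rated is the peer-delivered model itself. Appropriateness is secondary.

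**The concern.** McNemar's test and the paired t-test take their standard error from individual changes treated as independent. Pairing removes stable differences between leaders or villages, so those are not the problem. It does not remove a change that is shared by everyone a leader served.

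The design makes a shared change plausible. One leader hands over the kit, demonstrates it and sends the reminders, and the rating afterwards is of that delivery. The article's theory of change (Social Cognitive Theory, under Conceptual framework) also expects AGYW to be influenced by what their peers do and report.

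At stake are the p-values for average change in a primary outcome and in one secondary outcome. With a shared change they are too small, and a few unusually good or poor leaders could make an average gain or decline look significant.

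This is separate from the design effect of 1.0 in the sample-size calculation, which concerns the precision of a single proportion. Clustering by delivery would remain under simple random sampling of AGYW.

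**Working it through.** **The plan's own figures.** Sample size and sampling techniques: n0 = 1.96² × 0.5 × 0.5 / 0.05² = 384.16. With the finite population correction for 21,753 this is 384.16 / (1 + 384.16/21,753) = 377.5 (stated: 377), and 377 × 1.10 = 414.7, so 415. The figures reproduce. They target one proportion to ±5% and do not address a before-after test.

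**Inputs.** 30 leaders and 13 AGYW per leader (Implementation strategy). Alpha is 0.05; sidedness is not stated and two-sided is assumed. The ICC of the change is not in the article, so a range is assumed.

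**Formula.** With m AGYW per leader and leaders taken as random, the variance of the mean change is inflated by DE = 1 + (m − 1) × ICC. The true size of a nominal 5% independence test is then 2 × [1 − Φ(1.96/√DE)]. Example at ICC 0.05: DE = 1 + 12 × 0.05 = 1.60; 1.96/√1.60 = 1.55; size = 12.1%.

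**Simulation check.** 30 × 13 AGYW, zero mean change, random leaders, 20,000 runs, 40% discordant pairs.

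| ICC of change | DE | Size by formula | McNemar, simulated | t-test on 30 leader means, simulated |
|---|---|---|---|---|
| 0 | 1.00 | 5.0% | 4.7% | 4.9% |
| 0.01 | 1.12 | 6.4% | 6.4% | 5.2% |
| 0.02 | 1.24 | 7.8% | 7.6% | 5.0% |
| 0.05 | 1.60 | 12.1% | 12.4% | 5.3% |
| 0.10 | 2.20 | 18.6% | 19.0% | 5.1% |

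The paired t-test with Gaussian changes gives 5.0%, 6.3%, 12.2% and 18.7% at ICC 0, 0.01, 0.05 and 0.10. Using 20% or 60% discordant pairs at ICC 0.05 gives 12.5% and 12.6% for McNemar. The continuity-corrected McNemar test is slightly lower (11.1% at 0.05).

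**Where the error doubles.** A size of 10% needs 1.96/√DE = 1.645, so DE = (1.960/1.645)² = 1.42 and ICC = 0.42/12 = 0.035.

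**Sensitivity.**
- *Cluster size.* 30 × 13 = 390, not 415. With 415/30 = 13.8 per leader, the sizes are 6.5%, 8.0%, 12.6% and 19.4% at ICC 0.01, 0.02, 0.05 and 0.10.
- *Leaders as fixed.* If these 30 leaders are the whole target and their effects average zero, McNemar's simulated size is 4.5% at ICC 0.05 and 3.7% at 0.10: no inflation. The t-test on leader means is then conservative (1.3% and 0.3%).
- *Near the ceiling.* In a latent normal model (pre-post correlation 0.3, 6,000 runs), a leader share of 10% of the latent variance gives 10.4% rejection at 50% acceptability, 7.7% at 93% (ICC about 0.017) and 6.6% at 97% (ICC about 0.010). A 5% share gives 7.5%, 6.2% and 6.1%.

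**The case against.** The strongest objection is that the inflation is conditional. Leaders are chosen with the guidance of community leaders and CHWs, not sampled, and for these 30 leaders as fixed the planned tests hold their level. That stands as a condition. A reader might infer that the tests are invalid whenever leaders differ, and the article does not support that. It does state an aim wider than these 30: a model to be scaled up and used in similar settings (Abstract, Discussion). For that aim, variation between leaders belongs in the error term.

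Second, the size is unknown. No ICC is given, pairing already removes stable differences, and the Introduction cites very high willingness in other Ugandan AGYW groups (93% and 100%). Near the ceiling a given leader effect yields a smaller ICC. This also stands: a doubled error rate is possible but not established.

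Third, two further consequences might be inferred and are not supported. The article plans no confidence interval for the change, so there is no planned interval to call too narrow. Its sentence about guiding later large trials refers to the descriptive effectiveness results, not to these tests, and no progression rule depends on the p-value. The Abstract links pre- and post-intervention data to a future trial only in general terms.

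Fourth, this is a condensed article, the tests are to be used as appropriate, and an unseen analysis plan could add a cluster adjustment. That mitigates but does not answer the point. The article names the tests and the threshold, and confines multilevel modelling to a different analysis.

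**Conclusion.** The point holds in conditional form. As written, the tests of before-after change in AGYW-reported acceptability and appropriateness ignore delivery by a shared leader. Where changes are correlated within leader and the conclusion is meant to reach beyond these 30 leaders, the true error of the nominal 5% test is about 6.4% at ICC 0.01, 7.8% at 0.02, 12.1% at 0.05 and 18.6% at 0.10. It doubles only from about 0.035. At ICC 0, or with inference limited to these leaders, there is no inflation.

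Two limits remain. CHWs (ten) and parishes (five) sit above the leader and could also share change, so clustering on leader may not capture everything. For example, a parish ICC of 0.01 with 75 to 83 AGYW per parish would alone give about 14% to 15% by the same formula. The Mann-Whitney U test in the list, which is not a paired test, is a separate question not covered here.

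**What to change.** In Data management and analysis, replace the individual-level paired tests for AGYW outcomes with a paired analysis clustered on peer leader, and report the change with a 95% CI. Either of these would serve:

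- a one-sample t-test on the leader-level mean changes, with 29 df without parish, or 30 − 5 = 25 df if parish is a fixed stratum; or
- a mixed or GEE model of the outcome on time (before/after), clustered on leader, with a small-sample correction.

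Keep McNemar's test and the paired t-test as descriptive only.

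The link from each AGYW to her leader should not be assumed to exist. Post-intervention survey describes tracking kit counts over time, not who received a kit from whom; group meetings are one distribution route; and 415 − 390 = 25 surveyed AGYW have no evident leader. Record the assigned leader for each AGYW at distribution, and use village of residence as the cluster where none is assigned.

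The cost is a sentence or two of text, one recorded field and somewhat wider intervals. At ICC 0.05 the standard error is √1.60 = 1.26 times the independence value. If inference were confined to these 30 leaders, the leader-level test would be conservative.

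### The only rank test named for before-after change, Mann-Whitney U, is for independent samples, although the same AGYW are surveyed twice; the primary acceptability proportion is not affected

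*Protocol article*

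**What the plan says.** All references are to the protocol article.

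- **Baseline pre-intervention survey.** The 415 AGYW "will be selected from the five parishes using systematic random sampling at a household level and administered a baseline semi-structured survey". On content: "The questionnaire will also evaluate the feasibility, acceptability, and appropriateness of HIVST and the peer-delivered CHW-facilitated HIVST model".
- **Post-intervention survey.** After the intervention, "we will conduct a follow-up semi-structured survey with all the study participants using a semi-structured questionnaire".
- **Sample size and sampling techniques.** The minimum of 377 is raised by 10% to 415, partly to allow for loss to follow-up. That allowance presupposes that the same women are contacted again.
- **Data management and analysis.** On change over time: "We will also evaluate changes in the implementation outcomes before and after the intervention using paired t-test, Mann-Whiney U test" and McNemar's test, as appropriate, at p < 0.05. The same section foresees non-normal measures, to be summarised by "median and interquartile range for non-parametric distribution".
- **Study outcomes and Table 1.** AGYW acceptability, a primary outcome, is a proportion reported before and after implementation. Appropriateness is also a proportion. On the other primary outcome: "Feasibility is defined as the degree to which the HIVST is successfully distributed through the peer-delivered CHW-facilitated model"; Table 1 measures it as the share of planned kit distribution that is carried out.

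**The concern.** Mann-Whitney U compares two independent groups. Here each woman supplies both values, and the sentence concerns change over time. No independent comparison group is described for which the test would be right. The instruction to choose appropriately does not help, because it selects among three tests and none is a paired rank test. An analyst who meets a skewed or ordinal score and follows the text arrives at Mann-Whitney U.

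That test uses the variance of a difference between unrelated people. When repeat answers by the same person are positively correlated, this variance is too large: the test rejects too seldom under the null and misses real change that a paired test would detect.

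A smaller matter sits in the same sentence. It refers to the implementation outcomes without saying which of them have a baseline value. The surveys ask about feasibility before and after, but the feasibility defined as a primary outcome is kit distribution, which cannot exist before the intervention. A before-after p-value for feasibility would therefore describe perceived feasibility, under the name of the defined outcome.

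**Working it through.** **1. The plan's own figure.** Inputs from Sample size and sampling techniques: population 21,753, expected proportion 50%, margin ±5%, 95% confidence, design effect 1.0.

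- n0 = 1.96² × 0.5 × 0.5 / 0.05² = 384.16
- With finite population correction: 384.16 / (1 + 383.16/21,753) = 377.5, against the stated 377
- 377 × 1.10 = 414.7, against the stated 415

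Both figures reproduce. They rest on the precision of a single proportion, so the choice of pre-post test does not enter them.

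**2. True size of an independent-samples test on pairs.** With n pairs, common variance σ² and within-person correlation ρ, the mean difference has variance 2σ²(1 − ρ)/n. An independent-samples test assumes 2σ²/n. Its standardised statistic therefore has standard deviation √(1 − ρ) under the null, and

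size ≈ 2 × [1 − Φ(1.96/√(1 − ρ))].

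- ρ = 0.2: 1.96/√0.8 = 2.19, size 2.8%
- ρ = 0.5: 1.96/√0.5 = 2.77, size 0.56%

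**3. Simulation check.** 377 pairs; a latent bivariate normal cut into a 5-point item; 2,000 data sets per setting; two-sided 5%. The 5-point item, the correlations, the 0.15 SD latent shift and two-sidedness are assumptions; the documents give none of them.

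| Latent correlation | Size by formula | Size, Mann-Whitney | Size, signed-rank | Power, Mann-Whitney | Power, signed-rank |
|---|---|---|---|---|---|
| −0.2 | 7.4% | 7.0% | 4.8% | 52% | 46% |
| 0 | 5.0% | 5.6% | 5.5% | 50% | 50% |
| 0.2 | 2.8% | 2.7% | 5.0% | 50% | 57% |
| 0.3 | 1.9% | 1.8% | 4.6% | 48% | 62% |
| 0.5 | 0.6% | 0.5% | 4.4% | 48% | 74% |
| 0.7 | 0.03% | 0.1% | 4.7% | 48% | 91% |

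A separate simulation of 3,000 data sets at correlation 0.5 gave a size of 0.8% and power of 49% against 76%, hence the ranges quoted. Cutting the latent score into five categories lowers the observed correlation, so a size somewhat above the formula value is expected.

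**4. Which outcomes are exposed.** By Table 1, AGYW acceptability and appropriateness are proportions. A binary answer given twice by the same woman calls for McNemar's test, which is named. Mann-Whitney U could apply only to ordinal or skewed survey scores. Table 1 lists none, but the analysis section provides for medians and names a paired t-test, so such scores are possible.

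**The case against.** The strongest reply is that little depends on the error. The primary AGYW acceptability measure is a paired proportion with a correctly named test, the sample size is precision-based, and the effectiveness outcomes are to be reported descriptively. The 5-point item in the calculation is not an outcome in the documents. Under positive correlation the error is conservative, so it does not produce spurious claims of change. The test name may simply be a slip for the signed-rank test. All of this stands and limits the severity. It does not make the sentence right: the text names the wrong test, and nothing else in the article corrects it.

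Three stronger readings are tempting and are not supported.

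- **That p-values will be wrong and power lost in every case.** This depends on a within-person correlation that the documents do not give. At zero the two tests agree; at −0.2 Mann-Whitney is anti-conservative and rejects more often.
- **That ignoring clustering by parish or peer leader makes these tests invalid.** The article plans multilevel models for factors associated with acceptability, though not for the pre-post tests. Stable differences between parishes largely cancel in within-person change, and no effect on these tests has been quantified. Cluster-robust intervals would be unreliable with five parishes.
- **That fidelity and cost are to be tested before against after.** Fidelity is assessed by observational checklists and qualitative feedback, and cost from financial records with its own descriptive analysis. The general phrase about implementation outcomes is most naturally read as those measured at both surveys.

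**Conclusion.** The point holds in a limited form. The design yields paired data and the only rank test named assumes independent samples, so the rule is wrong as written for any ordinal or skewed pre-post score. For such a score, with 377 pairs and the assumptions shown above, Mann-Whitney would give up about 7 percentage points of power at latent correlation 0.2 (57 − 50) and about 26 to 27 at 0.5 (74 − 48; 76 − 49), with true size well below the nominal 5%. Positive correlation is likely for repeat answers by one person, but it remains an assumption.

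A reader might infer that the primary result or the sample size is compromised. Neither is. This is a should-fix correction of the analysis text.

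**What to change.** 1. In Data management and analysis, replace the Mann-Whitney U test with the Wilcoxon signed-rank test, and state that it is applied to each participant's linked pre- and post-intervention records.
2. State that pre-post tests apply only to measures collected at both surveys.
3. Report the survey's perceived feasibility under its own label, separately from the kit-distribution feasibility in Table 1, which has a post-intervention value only.

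The cost is a change of wording. No new data are needed: the paired t-test and McNemar's test already require the two surveys to be linked within person. The sample size stays as it is.

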**Methods:**

This mixed-methods quasi-experimental implementation science study will employ a three-fold approach. Firstly, we will conduct baseline formative qualitative research with 50 AGYW, 50 parents/partners to AGYW, 30 CHWs, 15 community leaders, and the district health office to inform the design of a peer-delivered CHW-facilitated HIV self-testing intervention tailored to AGYW’s needs in Northern Uganda. Secondly, we will implement a mixed-methods pilot study to assess the intervention’s feasibility and acceptability, involving 415 AGYW, 30 AGYW peer leaders, and 10 CHWs in selected parishes and villages in Omoro district, Northern Uganda. Lastly, we will evaluate the implementation outcomes and preliminary impact of the intervention on HIV self-testing rates and linkage to care by collecting and analyzing quantitative data pre- and post-intervention, laying the groundwork for a future robust randomized controlled trial.

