## Methods and materials

### Aims

The overall aim of this study is to establish a sustainable, community-based HIV self-testing model that effectively increases HIV rates and linkage to care among AGYW in Northern Uganda. The specific aims are:To develop a peer-delivered CHW-facilitated HIV self-testing model tailored to the needs of AGYW in Northern Uganda.To evaluate the feasibility and acceptability of the peer-delivered CHW-facilitated HIVST intervention in Northern Uganda.To assess the preliminary impact of the peer-delivered CHW-facilitated HIVST model on HIV self-testing rates and linkage to care among AGYW.

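### No stated analysis delivers the before-and-after evaluation of self-testing rates announced in the Abstract; testing is summarised only after kit receipt, apparently among recipients

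*Protocol article*

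**What the plan says.** The Abstract (Methods) describes the last phase of the study as evaluating implementation outcomes and "preliminary impact of the intervention on HIV self-testing rates and linkage to care by collecting and analyzing quantitative data pre- and post-intervention". The third specific aim, under Aims, is "To assess the preliminary impact of the peer-delivered CHW-facilitated HIVST model on HIV self-testing rates and linkage to care among AGYW"; it does not itself mention a before/after comparison.

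Study outcomes defines preliminary effectiveness, for testing, as "the proportions of AGYW who perform an HIV test within one month of HIVST kit reception". Post-intervention follow-up describes the data collection: "We will follow up with all the AGYW who received HIVST kits for up to one month to assess for self-reported use". Data management and analysis gives the modest sample, powered for acceptability, as the reason for a descriptive report, and continues: "we will provide descriptive findings on the proportion of AGYW that performed HIV testing after receiving HIVST kits".

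The same section plans paired and McNemar-type tests of change, but for implementation outcomes. Table 1 lists these as acceptability, feasibility, appropriateness, fidelity and cost.

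Two sources of data bear on change. At baseline, "Sociodemographic data, knowledge, perceptions, and practices on HIV and HTS, including HIVST, will be collected". After the intervention, "we will conduct a follow-up semi-structured survey with all the study participants", although testing practice is not among the topics named for that survey.

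**The concern.** A proportion counted from the day a kit is received has no counterpart before the intervention. However high it is, it cannot say whether testing rose, stayed level, or moved from facility tests to self-tests. The question announced in the Abstract therefore has no matching analysis, although baseline testing practices are collected and every participant is surveyed again.

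The second issue is the denominator. If only kit recipients are followed for use, women who were enrolled but not reached, or who declined a kit, do not count against uptake.

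The article says that these results will guide later controlled trials. A figure with no comparator and an unstated denominator is a weak basis for planning them. The primary outcomes, acceptability and feasibility, are not affected.

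**Working it through.** **1. The plan's own sample size.** Inputs from Sample size and sampling techniques: expected proportion 50%, margin ±5 points, 95% confidence, population 21,753, design effect 1.0, 10% added.

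- n0 = 1.96² × 0.25 / 0.05² = 384.15
- With finite population correction: 384.15 / (1 + 383.15/21,753) = 377.5, stated as 377
- 377 × 1.10 = 414.7, so 415

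Both figures reproduce. The sample size calculation is not at fault here.

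**2. Is there a before/after analysis of testing?**

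- Abstract: impact on self-testing rates, from pre and post data.
- Study outcomes: testing within one month after kit receipt, so post only.
- Post-intervention follow-up: kit recipients, by self-report, so post only.
- Data management and analysis: change is tested for implementation outcomes; testing uptake is reported descriptively after the kit.
- Table 1: testing uptake is not an implementation outcome.

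No listed analysis compares testing before and after.

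**3. Denominator.** Inputs: 30 peer leaders with 13 recipients each (Implementation strategy) and 415 enrolled (Sample size and sampling techniques).

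- Planned recipients: 30 × 13 = 390
- Planned coverage: 390/415 = 94.0%
- Ratio of uptake among recipients to uptake among all enrolled: 415/390 = 1.064. This assumes that non-recipients do not test and that no other route supplies kits to enrolled women.

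Illustration with an assumed 90% use among recipients:

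| Women who receive a kit | Uptake among recipients | Uptake among all 415 |
|---|---|---|
| 390 (as planned) | 90% | 0.90 × 390/415 = 84.6% |
| 351 (90% of plan) | 90% | 0.90 × 351/415 = 76.1% |
| 312 (80% of plan) | 90% | 0.90 × 312/415 = 67.7% |

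Only the first row uses the plan's own distribution figures; the other two show sensitivity.

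**4. Could the sample support an estimate of change?** Assumptions, none of them from the documents: 377 complete pairs, 20% start testing and 10% stop. The change is then 0.10 and the total discordance 0.30.

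- Half-width of the 95% interval: 1.96 × √((0.30 − 0.10²)/377) = 0.054, or 5.4 points
- At an assumed design effect of 2.5: 5.4 × √2.5 = 8.6 points
- McNemar power (normal approximation), no clustering: Φ[(0.10 × √377 − 1.96 × √0.30)/√0.29] = Φ(1.61), about 95%
- Power at design effect 2.5 (effective n = 377/2.5 = 150.8): Φ[(0.10 × √150.8 − 1.96 × √0.30)/√0.29] = Φ(0.29), about 61%

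Sensitivity: with pre and post status taken as independent, baselines of 43.4%, 50% and 84.4%, and rises of 5 to 15 points, the half-width is about 4 to 7 points without clustering. Multiplied by √2.5, that is about 6 to 11 points.

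**The case against.** The strongest reply is that the article is open about this. The analysis section calls the testing results descriptive, explains that the sample was powered for acceptability, and leaves effectiveness to later controlled trials. Testing uptake is neither a primary nor a secondary outcome. This stands: there is no hidden effectiveness test. What remains is that the Abstract describes an evaluation that the outcome definition and analysis do not provide.

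Several stronger readings are tempting, and the documents do not support them:

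- A reader might infer that Aim 3 itself promises a before/after comparison. It does not; that wording is in the Abstract, in a sentence that also covers implementation outcomes, and those do get before/after tests.
- A reader might infer that the plan fixes recipients as the denominator and so conceals poor reach. The outcome and analysis text do not spell out the denominator; it is inferred from who is followed. The share of planned distribution achieved is a feasibility measure in Table 1, so overall uptake could be partly reconstructed.
- A reader might infer that the sample is ample for testing change, so that the stated caution is unfounded. The 95% power holds only without clustering and falls to about 61% at the assumed design effect. Caution about a formal test is reasonable; it does not rule out an estimate with an interval.
- A reader might set the result against the Ugandan testing rates in the Introduction (43.4% to 84.4%). Those are general HIV testing rates with no stated recall period, so they are no comparator for self-testing within one month.

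Finally, even a paired change would be uncontrolled and could not establish cause. That also stands, and it governs how the change should be labelled.

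**Conclusion.** The point holds as a mismatch between the evaluation announced in the Abstract and the outcome and analysis given for testing. As written, the study cannot show a change in testing. This rests on reading the sections side by side and needs no numerical assumption.

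The denominator issue is smaller and conditional. Under the plan's own figures, recipient uptake exceeds uptake among all 415 by a factor of at least 1.06 (84.6% against 90% in the illustration), provided that recipients are the denominator, non-recipients do not test, and kits reach enrolled women only through the peer leaders.

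Precision of about 5 to 9 points under the assumed discordance is adequate for a descriptive estimate but not for a powered test. The discordance, the design effect and the 377 complete pairs are assumptions. The change is worth making because it is cheap and lets the study address the question it sets.

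**What to change.** 1. Put the same two questions (any HIV test; HIV self-test), with the same fixed recall period, in the baseline and post-intervention surveys. Report the paired change in each descriptively with a 95% interval, labelled as uncontrolled and not causal. Allow for clustering at village or peer-leader level, or use a small-sample correction, because five parishes are too few for a standard cluster-robust interval.
2. Report uptake with all enrolled AGYW as denominator and the among-recipients figure beside it, and state how women lost to follow-up are counted.
3. If no before/after comparison of testing is intended, reword the Abstract and Aim 3 to describe uptake after distribution among kit recipients.

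Cost: one aligned survey item, one extra table, and a lower headline uptake figure. Option 3 alone costs only a change of wording, but leaves the question of change unanswered.
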